### Sample size

In the PASSEM study, we chose the method suggested by Collins et al [22]. In this method, sample size calculation is based on the expected event rate (minimum of 100 events in all validation datasets). However, rules-of-thumb for sample size are problematic, as they are not specific to the model or validation setting. Indeed, Snell et al showed that the rule-of-thumb of having at least 100 events and 100 non-events does not always produce precise estimates of a model’s predictive performance measures [23]. To overcome this limitation, we chose to target an event rate of ≥200. Previous work by Freund et al [15] showed that a sample size of 879 patients yielded 74 events when power was set at 90%. Therefore, if we target a minimum of 200 events and consider 20% of lost to follow-up and missing data, a sample size of 2851 should be included. We will conduct an interim analysis after recruitment of 25%, 50%, and 75% of the target sample size to re-evaluate our assumptions and correct the sample size accordingly.

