**Methods and analysis:**

PASSEM study is an international prospective external validation cohort study. For 9 months, each participating center will recruit consecutive adult patients who visited the emergency departments with suspected infection and are planned for hospitalization. We will collect patients’ demographics, vital signs measured in the triage, initial white blood cell count, and variables required to calculate Charlson Comorbidities Index; and follow patients for 90 days since their inclusion in the study. The primary outcome will be 30-days in-hospital mortality. The secondary outcome will be intensive care unit (ICU) admission, prolonged stay in the ICU (i.e., ≥72 hours), and 30- as well as 90-days all-cause mortality. The study started in December 2021 and planned to enroll 2851 patients to reach 200 in-hospital death. The sample size is adaptive and will be adjusted based on prespecified consecutive interim analyses.

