#### Exclusion criteria

We will exclude patients who present to the ED due to non-infectious causes (e.g., autoimmune diseases, myocardial infarction, trauma, …etc.), pregnant woman, those who are transferred from other hospitals, or with “Do-Not-Resuscitate” (DNR) code status. Patients whose initial diagnosis of infection in the ED was not confirmed after the recruitment and follow-up will also be excluded (Box 1).

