#### Out-hospital follow-up

This phase starts if the patient is discharged from the hospital or 30-days have passed since inclusion to the study (whenever earlier; T_2_, maximum 90 days after T_0_) (Table 5). We will determine their status via telephone contact. We will also evaluate hospitalized patients’ situations by consulting their MRN in the recruiting center. We will consider a patient lost to follow-up if we cannot reach them via telephone contact by the end of this phase.

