### Statistical analysis

Continuous data will be reported as mean (SD) or median (IQR) and compared using unpaired *t* tests or analysis of variance and Mann-Whitney or Kruskal-Wallis test. Categorical variables will be expressed as number (percentage) and compared using a χ^2^ test or a Fisher exact test. We will begin by calculating an overall area under the receiver operating characteristic curve (AUC of ROC curve) and generate calibration curves of the qSOFA, SIRS, and EWSs to predict the primary and secondary outcomes. Subsequent to assessing the model’s overall performance; sensitivity, specificity, positive and negative predictive values will be calculated with cross tables for predicting primary and secondary outcomes for a qSOFA score of ≥2, SIRS of ≥2, and EWSs of ≥5. We will use the Kaplan-Meier method to estimate in-hospital and 90-day all-cause mortality. A log-rank regressions will be used to assess groups’ differences. Odd ratios (ORs) for in-hospital death, ICU admission, and 90-days all-cause mortality of qSOFA, SIRS, and EWSs will be estimated with a logistic regression analysis after adjustment for the patients’ demographics, comorbidities, and CCI. The model fit will be assessed by the calculation of the log-likelihood, Akaike information criterion (AIC), AUC, Bayesian information criterion (BIC), and D-statistics. To compare the performance of qSOFA, SIRS and EWSs, we will use absolute net-reclassification index (NRI). The absolute NRI mathematically represents a net proportion of patients correctly reclassified by one model as compared to another [24]. Net reclassification involves classifying patients in risk categories and determining how a new model reclassifies patients into various risk categories compared with a previous model. Risk differences are classified based on the actual outcome patients experienced (those who died vs those who did not).

A priori subgroup analyses will be conducted based on status of the following: COVID-19 (present vs absent), febrile neutropenia (present vs absent), solid organs or hematological cancers (present vs absent), autoimmune diseases (present vs absent), and severe comorbidities (CCI ≥3 vs <3), and race of the patient (Asian vs Black vs South Asian vs White) as permitted by sample size. If missing data is minimal (<5%) we will conduct a complete case analysis, otherwise we will use multiple imputation.

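### The allowance behind N = 2851 omits patients later excluded for unconfirmed infection, so 200 analysed deaths are expected only if losses from all causes total at most 16.7%

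*Protocol article*

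**What the plan says.** The Sample size section sets a target of at least 200 events. Its reason is that 100 events and 100 non-events do not always give precise estimates of predictive performance. It takes its event rate from an earlier cohort with 74 events in 879 patients and states that "if we target a minimum of 200 events and consider 20% of lost to follow-up and missing data, a sample size of 2851 should be" enrolled. The Abstract confirms that 2851 counts patients at entry: the study "planned to enroll 2851 patients to reach 200 in-hospital death".

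Entry rests on the emergency physician's suspicion of infection. Under Diagnosis of infection, two experts per centre review that diagnosis, where required, 30 days after inclusion. Box 1 lists failure to confirm as an exclusion criterion, and the Exclusion criteria section repeats it: "Patients whose initial diagnosis of infection in the ED was not confirmed after the recruitment and follow-up will also be excluded".

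Three other statements bear on the losses:

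- Out-hospital follow-up defines loss to follow-up by telephone contact: "We will consider a patient lost to follow-up if we cannot reach them via telephone contact by the end of this phase".
- In-hospital follow-up takes status from the recruiting centre's records. One possible status is transfer to another hospital.
- Statistical analysis handles missing data as follows: "If missing data is minimal (<5%) we will conduct a complete case analysis, otherwise we will use multiple imputation".

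The Sample size section also plans interim analyses at 25%, 50% and 75% of target recruitment, to revisit the assumptions and correct the sample size.

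**The concern.** The enrolment figure and the event target refer to different sets of patients. The 2851 are counted before infection is confirmed. The 200 deaths are needed in the set that is analysed, which by the plan's own rule excludes unconfirmed cases. Because entry depends on an opinion formed at presentation, some unconfirmed cases must be expected, and the exclusion rule presupposes them. Yet the only losses in the calculation are loss to follow-up and missing data.

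At stake is the minimum that the plan set for itself. Fewer analysed deaths mean wider intervals for sensitivity and less precise AUC and calibration estimates. The expected number of analysed deaths depends on a fraction that the document neither states nor budgets for.

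**Working it through.** **Inputs.** From the Sample size section: 74 events in 879 patients, a target of 200 events, a 20% allowance, and N = 2851. The unconfirmed fraction u is not in the document, so it is an assumption and is shown from 0% to 20%. The other loss d (loss to follow-up, missing data, outcomes not observed) is shown at 0%, 10% and the plan's 20%.

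**The plan's figure.** Event rate p = 74/879 = 0.08419. Patients to analyse = 200/0.08419 = 2375.7. Multiplied by 1.20 this is 2850.8, rounded up to 2851, an exact match. Dividing by 0.80 would give 2969.6, or 2970, so the 20% was multiplied on.

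**Break-even.** Total loss that still leaves 200 expected deaths = 1 − 2375.7/2851 = 16.7%, counting all causes. If d is 0%, 5% or 10%, then u can be at most 16.7%, 12.3% or 7.4%. If d is 20%, there is no room for any u.

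**Expected analysed deaths.** E = 2851 × (1 − d) × (1 − u) × 74/879. The chance of at least 200 deaths comes from the binomial distribution with 2851 × (1 − d) × (1 − u) patients and probability p. For example, with d = 10% and u = 10%, 2851 × 0.90 × 0.90 = 2309 patients and E = 194.4.

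| Other loss d | u = 0% | u = 5% | u = 10% | u = 15% | u = 20% |
|---|---|---|---|---|---|
| 0% | 240 (99.7%) | 228 (98%) | 216 (88%) | 204 (63%) | 192 (28%) |
| 10% | 216 (88%) | 205 (66%) | 194 (35%) | 184 (11%) | 173 (2%) |
| 20% | 192 (28%) | 182 (10%) | 173 (2%) | 163 (0.2%) | 154 (about 0) |

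Each cell gives expected deaths, with the chance of at least 200 in brackets.

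In the bottom row, the step from 200 to 192 at u = 0 comes from multiplying by 1.20 instead of dividing by 0.80. Only the further fall from 192 is due to unconfirmed infection.

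**Effect on precision.** The worst-case 95% half-width for sensitivity is 1.96 × √(0.25/E). It is 6.9 percentage points at 200 deaths, 7.5 at 173 and 7.9 at 154.

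**The case against.** The strongest reply is that the 20% may be larger than the loss it is named for. In-hospital deaths are read from the centre's records, telephone loss concerns the later phase, and missing data of 5% or more are imputed. If other losses are near zero, 2851 gives 240 expected deaths. The allowance then absorbs an unconfirmed fraction of up to 16.7%, and the defect is mainly one of labelling. The confirmation standard is also permissive: expert review takes place only where required, and equivocal evidence can be settled on clinical context. The fraction may therefore be small. All of this stands, and it is why the full table is needed and not only its bottom row.

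A reader might go further and infer that loss to follow-up does not touch the primary outcome at all. The document does not support that. Transfer to another hospital is a listed in-hospital status, and the recruiting centre's record may not show a later death elsewhere. The allowance is also not limited to the primary outcome, and 30- and 90-day all-cause mortality depend partly on telephone contact.

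The second reply is that the sample size is adaptive. This also stands in part. A reader might infer that the interim checks will overstate the event count because they are triggered by recruitment, but the trigger does not fix the denominator, and the text does not say which patients are counted. The checks could correct a shortfall if they work on confirmed patients. The text does not say so, Box 1 places the exclusion after recruitment and follow-up, and patients recruited in the 30 days before a look will not have reached day-30 review.

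Finally, 200 is an event-count target, not a computed precision requirement, and the loss of precision over the range shown is moderate.

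**Conclusion.** The point holds as a mismatch between the stated sample size and the plan's own exclusion rule. The allowance leaves out a loss that the plan itself prescribes, and 2851 yields 200 expected analysed deaths only if losses from every cause total at most 16.7%. Whether that condition is met cannot be judged from the document. With no other loss, the chance of reaching 200 runs from 98% at 5% unconfirmed to 28% at 20%. With 10% other loss it runs from 66% to 2%, and with the full 20% from 10% to about zero.

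A reader might infer that the study will miss its target. The document does not support that, because it gives no unconfirmed fraction and allows the sample size to be corrected. A reader might also turn the shortfall into a loss of power. That is not supported either: the 90% power mentioned belongs to the earlier cohort, and this plan makes no power claim at 200 events.

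The figures rest on 8.42% mortality among confirmed patients. The document does not say whether the 879 reference patients were counted before or after a similar exclusion. The mismatch is worth correcting because the study relies on this figure, but its likely effect on precision is moderate.

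**What to change.** In the Sample size section:

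1. Name unconfirmed infection as a component of the allowance, with an assumed fraction and its basis.
2. State the expected number of analysed 30-day in-hospital deaths at 2851 over a plausible range of that fraction, as in the table above.
3. Define the 200-death target, and the event rate used at the three interim checks, on patients whose infection status has been settled (day-30 review completed where required) and is confirmed.
4. Keep an allowance for primary outcomes that may go unobserved after transfer to another hospital.

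The cost is a change of wording and a restated event count. Confirmation is already scheduled for day 30, so no new data are needed. The stated event count may look less favourable. The restatement itself requires no extra patients; whether to enrol more remains a decision for the interim checks.

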### Study outcome

The primary outcome of this study is 30-days in-hospital mortality. Secondary outcomes include ICU admission (within 30-days), ICU length of stay, and all-cause mortality within 30 and 90 days.

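### At the plan's own 20% attrition, 2851 patients give about 192 expected deaths rather than 200, because the allowance was multiplied in (x 1.20) instead of divided out (/ 0.80)

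*Protocol article*

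**What the plan says.** The event counted is in-hospital death within 30 days (Study outcome: "The primary outcome of this study is 30-days in-hospital mortality"). The Sample size section takes its event rate from an earlier cohort, in which "a sample size of 879 patients yielded 74 events when power was set at 90" per cent. It rejects 100 events as too few, doubles the target to at least 200, and gives the result as: "consider 20% of lost to follow-up and missing data, a sample size of 2851 should be included". The Abstract repeats the result as a plain commitment ("planned to enroll 2851 patients to reach 200 in-hospital death"), and Table 4 carries the same total.

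Two other provisions bear on the point. The sample size may be revised: "We will conduct an interim analysis after recruitment of 25%, 50%, and 75% of the target sample size to re-evaluate our assumptions". For incomplete data, the Statistical analysis section says: "If missing data is minimal (<5%) we will conduct a complete case analysis, otherwise we will use multiple imputation".

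**The concern.** An allowance for attrition should leave the required number of patients after the losses have occurred. If a fraction d of those enrolled is lost, the required number must be divided by (1 - d). Multiplying by (1 + d) falls short, and the gap grows with d. At 20% the two answers differ by about 4%.

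At stake is whether the published size claim follows from its published inputs. The section adopts 200 events because it judges the 100-event rule of thumb unreliable, so the 200 is the whole justification for the sample size. A reader who takes the stated rate and the stated attrition should be able to arrive at 200, and cannot.

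**Working it through.** **Inputs, all from the Sample size section**
- Target: 200 deaths
- Event rate: 74/879 = 0.084187 (8.42%)
- Loss to follow-up and missing data: 20%

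**Reproducing the plan's figure**
- Analysable patients needed: 200 / 0.084187 = 2375.7
- Multiplied by 1.20: 2375.7 x 1.20 = 2850.8, rounded up to **2851**. This is the stated figure exactly.

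**Inflation that matches a 20% loss among those enrolled**
- 2375.7 / 0.80 = 2969.6, rounded up to **2970**
- Difference: 2970 - 2851 = 119 patients
- Check: 2970 x 0.80 x 0.084187 = 200.0 expected deaths

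**What 2851 delivers under the plan's own assumptions**
- Analysable: 2851 x 0.80 = 2280.8
- Expected deaths: 2280.8 x 0.084187 = **192.0**, which is 8 below 200 (8/200 = 4%)
- Attrition at which 2851 still gives 200: 1 - 2375.7/2851 = **16.7%**
- If nobody leaves the analysis: 2851 x 0.084187 = 240.0 expected deaths

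**How much this matters**
- Precision varies roughly with the square root of the number of events: sqrt(200/192) = 1.02, so intervals are about 2% wider.
- The binomial chance of at least 200 deaths is about 28% with 2280 analysable patients and about 51% with 2376 (the number left from 2970). Even the correct inflation reaches 200 only about half the time, because 200 is the mean and not a floor.
- The borrowed rate is itself uncertain. The 95% Wilson interval for 74/879 is about 6.8% to 10.4%, which with 2281 analysable patients spans roughly 154 to 238 deaths. That spread is much larger than the 8 deaths at issue.

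No significance level, power or effect size enters any of these steps.

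**The case against.** **The 20% may not leave the primary analysis.** This is the strongest objection. Once missing data reach 5%, the plan imputes rather than deletes. Under Out-hospital follow-up, a patient counts as lost only when telephone contact fails by the end of that phase, whereas in-hospital status is read from the hospital record (In-hospital follow-up). Such losses therefore bear mainly on the all-cause mortality outcomes. This part stands: a reader might infer that the study will end with only 192 deaths, and the documents do not support that. It does not rescue the stated figure, because the Sample size calculation itself treats the 20% as needing replacement. If those patients are to be retained, the allowance needs a different rationale.

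**The 20% may have been meant relative to analysable patients.** The multiplication would then be consistent, and the true attrition among those enrolled would be 0.20/1.20 = 16.7%. The text does not say this, and the ordinary reading is 20% of those enrolled.

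**The interim analyses will correct it.** They could, since observed deaths and losses will be known. A reader might go the other way and infer that the interims will repeat the error. The article gives no re-estimation formula, so neither can be asserted. As the text stands, what is to be revisited is the assumptions; nothing addresses the inflation step.

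**Two further readings go too far.** The mention of 90% power describes the earlier cohort; it claims no power for this study and is merely superfluous. Patients excluded later because infection was not confirmed (Exclusion criteria, Box 1) could reduce the count further, but the article gives no rate for them and does not say whether the 2851 is counted before or after that exclusion. No size can be put on this.

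**Conclusion.** The sample size statement is wrong as written, and the error is minor. From the plan's own inputs, 2851 corresponds to about 192 expected deaths, not 200; the number matching 200 is 2970. The conclusion rests on three assumptions: that the 20% refers to enrolled patients, that they leave the primary analysis, and that their leaving is unrelated to death. To the extent that they stay in, the shortfall shrinks, and it vanishes once attrition is 16.7% or less.

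The size is 8 events, or 4% of the target. No decision rule in the article turns on 192 as against 200, and the uncertainty in the borrowed event rate is far greater. The error does not threaten the study's conclusions. It does make the headline claim in the Sample size section and the Abstract untrue under its own assumptions.

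**What to change.** 1. In the Sample size section and the Abstract, state that 2851 enrolled patients give about 192 expected deaths at 20% attrition, or 200 if attrition is no more than 16.7%.
2. Describe 200 as an expected count, not a guaranteed minimum.
3. At the 25%, 50% and 75% re-estimations use N = 200 / [observed event rate x (1 - observed proportion leaving the primary analysis set)]. With the present inputs this gives 200 / (0.084187 x 0.80) = 2970. Count patients excluded later for unconfirmed infection in that proportion if they are included in the 2851.
4. Optionally delete the reference to 90% power, which plays no part in the calculation.

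The cost is a few sentences and one formula. Restating the figures requires no extra patients and changes no study procedure; the stated event count becomes slightly less favourable. Keeping 200 expected deaths at a true 20% attrition would mean enrolling 119 more patients, and the interim data can show whether that is needed.

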### Statistical analysis

Continuous data will be reported as mean (SD) or median (IQR) and compared using unpaired *t* tests or analysis of variance and Mann-Whitney or Kruskal-Wallis test. Categorical variables will be expressed as number (percentage) and compared using a χ^2^ test or a Fisher exact test. We will begin by calculating an overall area under the receiver operating characteristic curve (AUC of ROC curve) and generate calibration curves of the qSOFA, SIRS, and EWSs to predict the primary and secondary outcomes. Subsequent to assessing the model’s overall performance; sensitivity, specificity, positive and negative predictive values will be calculated with cross tables for predicting primary and secondary outcomes for a qSOFA score of ≥2, SIRS of ≥2, and EWSs of ≥5. We will use the Kaplan-Meier method to estimate in-hospital and 90-day all-cause mortality. A log-rank regressions will be used to assess groups’ differences. Odd ratios (ORs) for in-hospital death, ICU admission, and 90-days all-cause mortality of qSOFA, SIRS, and EWSs will be estimated with a logistic regression analysis after adjustment for the patients’ demographics, comorbidities, and CCI. The model fit will be assessed by the calculation of the log-likelihood, Akaike information criterion (AIC), AUC, Bayesian information criterion (BIC), and D-statistics. To compare the performance of qSOFA, SIRS and EWSs, we will use absolute net-reclassification index (NRI). The absolute NRI mathematically represents a net proportion of patients correctly reclassified by one model as compared to another [24]. Net reclassification involves classifying patients in risk categories and determining how a new model reclassifies patients into various risk categories compared with a previous model. Risk differences are classified based on the actual outcome patients experienced (those who died vs those who did not).

A priori subgroup analyses will be conducted based on status of the following: COVID-19 (present vs absent), febrile neutropenia (present vs absent), solid organs or hematological cancers (present vs absent), autoimmune diseases (present vs absent), and severe comorbidities (CCI ≥3 vs <3), and race of the patient (Asian vs Black vs South Asian vs White) as permitted by sample size. If missing data is minimal (<5%) we will conduct a complete case analysis, otherwise we will use multiple imputation.

For all analyses, a 2-tailed *P* <0.05 will be considered statistically significant. Statistical analyses will be performed with Stata version 17.0 [25] and RStudio version ‘2022.7.0.548’ [26].

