#### In-hospital follow-up

Once enrolment is completed, the in-hospital follow-up phase will start (T_1_, maximum 30 days after T_0_) (Table 5). Study team will monitor hospitalized patients’ status (i.e., death, alive and either discharged, transferred to another hospital, or still hospitalized) by consulting their specific medical registration number (MRN) in the recruiting center.

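### Kaplan-Meier and log-rank are planned for in-hospital mortality, where discharge alive is a competing event; if discharge is censored, the curve overstates 30-day in-hospital mortality

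*Protocol article*

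**What the plan says.** In the protocol article, Statistical analysis, one sentence assigns the same method to two endpoints: "We will use the Kaplan-Meier method to estimate in-hospital and 90-day all-cause mortality". The next begins "A log-rank regressions will be used to assess" and refers to differences between groups. No competing-risk method is named, and nothing says how patients discharged alive enter the in-hospital curve.

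Under Study outcome: "The primary outcome of this study is 30-days in-hospital mortality". The in-hospital phase runs to at most 30 days after enrolment, and In-hospital follow-up lists the patient states to be monitored as "death, alive and either discharged, transferred to another hospital, or still hospitalized". Out-hospital follow-up then continues to day 90: "This phase starts if the patient is discharged from the hospital or 30-days have passed since inclusion to the study".

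The Statistical analysis section also treats in-hospital death as a fixed yes/no outcome in the AUC, the cross tables, the logistic regression and the net reclassification index.

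**The concern.** Kaplan-Meier estimates cumulative risk correctly when censored patients remain capable of the event and have the same later risk as those still observed. Neither condition holds for in-hospital death when patients are censored at discharge. They can no longer die in hospital during that admission, and they usually leave because they have recovered. The estimator nevertheless treats them as if they would have gone on dying at the rate seen in patients still in hospital.

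The resulting curve would overstate 30-day in-hospital mortality. It would sit beside cross tables and logistic models built on the simple 30-day proportion, so one report would carry two different mortality figures for one endpoint. The log-rank test on the same data would compare the rate of death among patients still in hospital. That is a legitimate quantity, but it is not the cumulative in-hospital mortality that the primary outcome names.

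**Working it through.** **Inputs from the document.** The expected event rate comes from Sample size: "a sample size of 879 patients yielded 74 events when power was set at 90" per cent, so 74/879 = 0.0842. The horizon is 30 days.

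**Reproducing the plan's own figure.** 200 / (74/879) = 2375.7, and 2375.7 × 1.2 = 2850.8, rounded up to 2851. This matches the stated sample size, so 8.42% is the in-hospital mortality that the plan works with.

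**Inputs not in the document (assumptions).** Length of stay, timing of deaths, and censoring at discharge.

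**Constant hazards.** Let h be the total rate of leaving hospital, dead or alive, with h = ln 2 / median stay. Choose the death hazard d so that the true cumulative incidence at day 30 is 0.0842:

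- d = 0.0842 × h / (1 − exp(−30h))
- Kaplan-Meier with discharge censored: 1 − exp(−30d)

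| Assumed median stay | h | d | 30d | 1 − KM | Ratio to 8.42% |
|---|---|---|---|---|---|
| 5 days | 0.1386 | 0.01186 | 0.356 | 29.9% | 3.6 |
| 7 days | 0.0990 | 0.00879 | 0.264 | 23.2% | 2.8 |
| 10 days | 0.0693 | 0.00667 | 0.200 | 18.1% | 2.2 |

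**Varying the timing of deaths.** Here the discharge hazard is constant, with an assumed mean time to discharge, and the death hazard is scaled so that the true figure stays at 8.42%. Entries are the ratio of 1 − KM to the true value.

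| Death hazard | Mean 5 days | Mean 10 days | Mean 14 days |
|---|---|---|---|
| Halves every 3 days | 1.8 | 1.4 | 1.3 |
| Halves every 7 days | 2.7 | 1.9 | 1.6 |
| Constant | 5.0 | 3.0 | 2.3 |
| Doubles every 14 days | 7.5 | 4.1 | 3.0 |

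The direction is the same in every cell. The size runs from 1.3-fold to 7.5-fold.

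**Alternative handling.** A simulation of 118,800 patients with constant hazards and a mean time to discharge of 10 days gave:

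- crude 30-day in-hospital mortality: 8.35%
- Kaplan-Meier censoring at discharge: 24.7%
- Kaplan-Meier keeping discharged patients event-free at risk to day 30: 8.35%

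So the bias comes from the risk set, and it disappears when discharged patients stay in it.

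**The case against.** The strongest reply is that the article never says patients are censored at discharge. Follow-up continues to day 90, so keeping them event-free to day 30 is feasible, and Kaplan-Meier then returns the crude proportion. A censoring rule is also the kind of detail that a condensed article may leave to an analysis plan. This stands as far as it goes, and it makes the conclusion conditional. It does not remove the point. The article names the method, applies it without distinction to an endpoint that discharge precludes and to one that it does not, and under the usual handling the result is wrong.

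Four stronger readings are tempting, and the document does not support them:

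- **A fixed inflation factor, such as two- to three-fold.** The document gives neither length of stay nor timing of deaths. The constant-hazard examples alone span 2.2 to 3.6, and the wider assumptions span 1.3 to 7.5.
- **That the log-rank test is invalid or inherits the curve's inflation.** With discharge censored, it validly tests cause-specific hazards of in-hospital death. The problem is that this is a different quantity from cumulative in-hospital mortality. Any distortion between score groups would depend on length of stay by score, which is not given.
- **That deaths after transfer are lost from the primary outcome.** In-hospital follow-up only lists transfer as a recorded status. Nothing says that later deaths in the receiving hospital are excluded, and nothing says that place of death is collected. No change on transfers is proposed here.
- **That the study's main conclusions are at risk.** The AUC, sensitivity and specificity, logistic regression and net reclassification analyses do not use the in-hospital curve. Neither does the sample size, and the 90-day all-cause curve is sound.

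**Conclusion.** The point holds in conditional form, with moderate severity. Discharge alive is a competing event for in-hospital death. If it is censored, the planned curve overstates 30-day in-hospital mortality and contradicts the proportions used elsewhere in the same section, and the log-rank test addresses cause-specific hazards.

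As an illustration, a true 8.4% would be reported as about 30%, 23% or 18% at assumed median stays of 5, 7 or 10 days. These figures rest on constant hazards and on censoring at discharge, neither of which the document states. Early deaths reduce the excess, and keeping discharged patients event-free at risk to day 30 removes it. What is exposed is the in-hospital curve and its group comparison, not the accuracy results.

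**What to change.** In Statistical analysis, separate the two endpoints:

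- **30-day in-hospital mortality:** estimate the cumulative incidence function (Aalen-Johansen) with discharge alive as the competing event, and compare groups with Gray's test. Alternatively, keep discharged patients event-free in the risk set to day 30 and say so.
- **30- and 90-day all-cause mortality:** keep Kaplan-Meier and log-rank.

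The cost is a few sentences of analysis wording. Discharge status is already monitored during the in-hospital phase, so the change needs no new type of data, and the sample size and accuracy analyses stay as they are.
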